## Abstract

**Background:**

Stroke in adults aged between 18 and 64 years old is increasing significantly worldwide. Studies have reported that this group of young stroke survivors encounters enormous difficulties reintegrating into their social roles. Individualised discussions with healthcare professionals and learning from other survivors are imperative for them to reconstruct their identities after stroke. There is also great demand for community support during their chronic stage of recovery to help them rebuild life skills to promote reintegration.

**Methods/design:**

This is a randomised controlled trial to investigate the effects of a 24-week Narrative and Skills-building Intervention (NSI) on young stroke survivors’ community reintegration and psychosocial outcomes. A total of 208 adults aged 18–64 years old with a first-ever or recurrent ischaemic or haemorrhagic stroke and have been discharged home will be recruited and randomly assigned to receive usual care or usual care with NSI. The NSI is grounded in Narrative Theory and Bandura’s principles of Self-efficacy and Outcome Expectation, consisting of successive eight individual sessions over six months delivered by a trained facilitator (a registered nurse). Participants will be facilitated to narrate their survival experiences and rebuild core life skills. Videos of peer young stroke survivors’ experiences of recovery will be provided. Outcomes including community reintegration, depressive symptoms, health-related quality of life, self-efficacy, outcome expectation and satisfaction with performance of self-management behaviours will be measured before (T0) and immediately after NSI (T1), then six (T2) and 12 months after NSI (T3). Generalised estimating equations models will be used to compare the differential changes in outcomes across time between the two groups. Focus group interviews will be conducted with the facilitator at T1 and with the participants in the intervention group at T1 and T3.

**Discussion:**

This study will evaluate the short and long-term effects of a theory-based NSI on young stroke survivors’ community reintegration and establish a new model of community reintegration after stroke to inform future research. The results will also provide valuable evidence to develop clinical guidelines for young stroke survivors’ community reintegration.

**Trial registration:**

ClinicalTrials.gov identifier: NCT04560140, registered on 23 September, 2020.

**Supplementary Information:**

The online version contains supplementary material available at 10.1186/s12883-020-02015-5.

## Background

The global prevalence of stroke in adults aged 20–64 years old doubled from 1990 to 2013 [1]. International guidelines recommend promoting community reintegration as a rehabilitation priority for stroke survivors [2, 3]. Community reintegration refers to one’s ability to resume or adapt one’s roles and responsibilities and to actively participate in social activities after a disabling illness [4]. Studies have reported that this group of young adults with stroke encounters substantially greater difficulties reintegrating into their social roles compared to older adults. Common challenges include maintaining family relationship and a social network, resuming leisure activities, or returning to work [5, 6]. Age-appropriate interventions to facilitate young stroke survivors’ acceptance of their functional limitation and development of life skills to reconstruct their roles for better community reintegration are warranted.

Previous studies have consistently reported the complex and chronic nature of young stroke survivors’ community reintegration [5–8]. A review of the literature on survivors aged 18–65 years old found that the abrupt onset of stroke was often stigmatised as a disease of old age, and that their ability to perform self-care activities was consequentially compromised, which significantly disrupted their sense of self, role and relationship. They had a loss of control and an increased sense of uncertainty in their life after stroke [5]. A qualitative study of 17 community-dwelling survivors aged 23–55 years old reported that they might develop an adapted sense of self several years after the stroke event. However, it has been suggested that these survivors need guidance and support to reflect on their experiences, re-appraise their strengths and re-adjust their personal values to re-construct their identities and roles [6]. A qualitative study of 22 stroke survivors who were aged 20–61 years old and about six months to nine years after stroke found that their struggles of inability to fulfil their role expectations or maintain intimate relationships resulted in emotional shortcomings such as feelings of isolation or helplessness. The results highlighted the need for providing survivors with opportunities to narrate their experiences outside their homes and offering support in the later phase of recovery to prevent psychosocial problems [7]. Another study of 12 women aged 18–50 years old has also highlighted the young stroke survivors’ unmet needs, including a lack of access to age-appropriate information, inadequate professional support regarding life skills training, limited dialogue with healthcare professionals and underuse of peer learning to support the continual reintegration process [8].

Personal or illness experience narratives have been examined in previous studies to help stroke survivors re-establish their identity and roles through meaning-making, bridging between the present situation and the ideal future life, and exploring opportunities for change [9–11]. A feasibility study of 17 survivors aged 33–89 years old reported that those receiving a nurse-led intervention using narratives appreciated the opportunities to share and re-create their stroke experience with a healthcare professional. Following Narrative Theory, the participants were supported to reflect on their experience through this act of narrating. The narrative facilitated their reflection and self-understanding. It stimulated them to envision for future changes and make adjustment in their lives after stroke [10]. A one-group study of 27 survivors aged 44–73 years old with post-stroke aphasia found that a biographic-narrative intervention was associated with potential benefits in health-related quality of life (HRQoL) and mood at three months post-intervention. Participants were asked to share their daily life experiences after stroke to reshape their identity. They were also facilitated to learn from peers and increase social contact via discussing health or leisure time issues during group sessions [11].

Skills-building is vital to improve stroke survivors’ ability to plan, solve problems and set personal goals for better community reintegration [12]. Three experimental studies examined the effects of self-management interventions aimed at promoting participation in daily life after stroke. The interventions, led by an occupational therapist, focused on home modifications and developing survivors’ self-management skills, including problem solving, decision making, action planning, resource utilisation and partnership with care providers [13–15]. Among the studies, one randomised controlled trial (RCT) of 185 adults with mild to moderate stroke found significant improvements in health-related and participation self-efficacy in daily life activities immediately after completing the 12-session group and community-based intervention [13]. A follow-up quasi-experimental study of 17 survivors found significant improvement in community reintegration upon completion of a 6-session intervention enriched with components for problem solving and goal setting [14]. A randomised pilot study of 15 survivors also reported a clinically meaningful change in social participation at six months after receiving a participation-focused individual-based programme that included one pre-discharge and five post-discharge home visits [15]. Several systematic reviews have suggested that problem-solving skills are likely to facilitate self-management after stroke [12, 16, 17]. Contrastingly, an RCT of 62 stroke survivors reported significant improvements in depressive symptoms and anxiety among those who received a solution-focused therapy compared with the control group [18]. Two qualitative studies of 12 stroke survivors also suggested doing everyday activities at home developed skills in managing role changes through mastery experiences and negotiation with spouses [19, 20].

There have been limited studies that examined interventions for promoting community reintegration after stroke, and young stroke survivors are often under-represented in these studies. Moreover, grounding the design, development and evaluation of such a complex intervention in a theoretical framework is important to explain the mechanisms underlying the changes in outcomes [21]. More investigations on the best theoretical frameworks that consider a person’s interpretation of experiences and self-efficacy relating to behavioural change are needed. There are an increasing number of studies that have used narratives as an approach to help stroke survivors to understand their experience of stroke and have showed positive results for psychological well-being. More evidence on the effects of using narratives in promoting the community reintegration of young stroke survivors would be worthwhile. Young stroke survivors need to develop life skills to address their internal struggles and the challenges they encounter during the return to their family and social roles. There has been no consensus, however, on the core skills for promoting community reintegration in young stroke survivors.

This study aims to investigate the effects of a 24-week Narrative and Skills-building Intervention (NSI) on community reintegration, self-efficacy, outcome expectation, satisfaction with performance of self-management behaviours and psychosocial outcomes among young stroke survivors. We hypothesise that the participants in the intervention group, compared with the control group, will demonstrate all of the following at immediately, 6 months and 12 months post-intervention: a) Significant increase in community reintegration with respect to baseline; b) Significant improvements in depressive symptoms, HRQoL and satisfaction with performance of self-management behaviours with respect to baseline, and c) Significant increases in self-efficacy and outcome expectation of performing self-management behaviours with respect to baseline.

## Methods/design

### Study design

A multi-centred, assessor-blinded, two-arm RCT will be conducted. The outcomes will be measured at baseline (T0), immediately post-intervention (T1), and 6 months (T2) and 12 months post-intervention (T3) (Fig. 1).

**Fig. 1 Fig1:**
[figure not shown]
Study flow diagram

### Setting

Participants will be recruited from three acute public hospitals, and community-based organisations serving people with chronic conditions including stroke in Hong Kong. The three hospitals follow the same stroke care pathway endorsed by the Hong Kong Hospital Authority. All sessions of the NSI and all of the assessments will be conducted in the participant’s homes or a community centre.

### Participants

Individuals will be recruited if they: (1) are 18–64 years of age, (2) have a clinical diagnosis of first-ever or recurrent ischaemic or haemorrhagic stroke, (3) are living at home after discharge from hospital, (4) have a Montreal Cognitive Assessment (MoCA) score > 2nd percentile, (5) have a modified Rankin Scale (mRS) score ≥ 3 (moderate disability), (6) can communicate in Cantonese, and (7) are able to attend all NSI sessions.

Individuals will be excluded if they 1) have been diagnosed with transient ischaemic attack, subdural or epidural haemorrhage [22], 2) have experienced cerebrovascular events due to tumours or head trauma, 3) have been diagnosed with a mental condition such as depression, schizophrenia, bipolar or personality disorder, 4) demonstrate incomprehensible speech or difficulty in comprehending conversations, or 5) have received a self-management programme in the past.

### Sample size estimation

The sample size is estimated based on the outcomes of community reintegration, self-efficacy and outcome expectation. In our previous interventional study [23], the effect sizes of a stroke self-management programme on community reintegration, self-efficacy and outcome expectation of performing self-management behaviours were 0.44, 0.55 and 0.53, respectively. Using the power analysis software PASS 16 (NCSS, LLC. Kaysville, Utah, USA), a sample size of 83 participants per study arm is estimated to give this two-arm RCT 80% power at a two-sided 5% level of significance to detect an effect size as small as 0.44 on the primary outcome between the control and intervention groups at a post-intervention time point. Further allowing for a potential attrition rate of up to 20%, 208 participants, with 104 per group, will be recruited.

### Randomisation and blinding

The participants will be randomly allocated to either the intervention (I) or the control (C) group at 1:1 ratio after they have provided consent and baseline data. Block randomisation in blocks of ten, except the last block, will be used. An independent statistician will generate a random sequence of grouping identifiers (I or C) using a random list generator (www.randomization.com). According to the sequence, a grouping identifier will be placed into an opaque, identical, sealed and sequentially numbered envelope for concealed allocation. All participants will be pooled into the same enrolment list regardless of their recruitment venues. A research assistant will open the envelopes sequentially according to the participants’ time of enrolment and record the grouping. Another research assistant who will conduct the baseline and follow-up assessments and data entry will have no knowledge of the participants’ group assignments. Blinding is not possible for the participants and the facilitator who will deliver the NSI, due to the nature of the intervention. The research assistant, who will conduct qualitative evaluation with the facilitator and participants’ feedback on the NSI, will know the group allocations.

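### A published, fixed block size of ten lets anyone who sees every allocation deduce about 35 of 208 in advance, and the article does not separate the envelope opener from the screener

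*Protocol article*

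**What the plan says.** All of the allocation rules stand in the section Randomisation and blinding.

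- **Block size:** "Block randomisation in blocks of ten, except the last block, will be used".
- **Ratio and timing:** allocation is "at 1:1 ratio after they have provided consent and baseline data".
- **One sequence:** "All participants will be pooled into the same enrolment list regardless of their recruitment venues".
- **Concealment:** an independent statistician generates the sequence, and each group label is "placed into an opaque, identical, sealed and sequentially numbered envelope for concealed allocation".
- **Who sees the sequence:** "A research assistant will open the envelopes sequentially according to the participants’ time of enrolment and record the grouping".
- **Who assesses:** "Another research assistant who will conduct the baseline and follow-up assessments and data entry will have no knowledge" of the assignments.
- **Who cannot be blinded:** the participants and the facilitator.

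The total comes from Sample size estimation: "208 participants, with 104 per group, will be recruited".

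The section Data collection says that a research assistant visits the venues, screens, telephones candidates and makes the preliminary eligibility assessment. It does not say whether this is the person who opens the envelopes, the blinded assessor or someone else.

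**The concern.** Sealed envelopes stop staff from reading the next allocation. They do not stop staff from working it out. If every block holds exactly five of each group and the size is known, then once five of one group have appeared, the rest of the block is fixed. The size is printed in a published article, so it has to be treated as known to everyone on the team.

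Foreknowledge does harm only if it reaches someone who decides who enters and when. Envelopes are used in order of enrolment, so the person who approaches candidates or books baseline visits influences which candidate meets which envelope. Two eligibility rules under Participants call for judgement: whether the candidate can attend every session, and whether the candidate has trouble following a conversation. A screener who expects a given arm could apply them more strictly or more loosely without intending to.

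The comparison would then be between groups selected differently at entry. Blinding the assessor does not repair this. The participants know their group, and the primary outcome, the reintegration index, is their own rating.

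**Working it through.** **Inputs.** Block size 10, ratio 1:1 and a single list (Randomisation and blinding); 208 participants, 104 per group (Sample size estimation).

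**1. The plan's own total.** For an effect size of 0.44 at a two-sided 5% level, the two-sample t calculation gives power 0.7997 with 82 per arm and 0.8045 with 83, so 83 per arm is right. With 20% attrition, 83 / 0.8 = 103.75, rounded up to 104, and 2 × 104 = 208. This reproduces.

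**2. Block structure.** 208 = 20 × 10 + 8. Twenty full blocks use 100 per arm, which leaves 4 per arm for a last block of 8. That agrees with the exception made for the last block.

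**3. Allocations that can be deduced with certainty.** In a balanced block of size 2m, these are the final run of identical labels. Its expected length is 2m / (m + 1), confirmed by listing every possible block (252 for size ten).

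- Size 10 (m = 5): 10 / 6 = 1.667
- Size 8 (m = 4): 8 / 5 = 1.600
- Whole trial: 20 × 1.667 + 1.600 = 34.93, and 34.93 / 208 = 16.8%

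**4. Best guessing.** The strategy is to guess the arm that has appeared less often so far, and to toss a coin when the arms are level. Expected correct guesses per block are m + (4^m / C(2m, m) − 1) / 2.

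| Block size | Correct per block | Success |
|---|---|---|
| 4 | 2.833 | 70.8% |
| 6 | 4.100 | 68.3% |
| 8 | 5.329 | 66.6% |
| 10 | 6.532 | 65.3% |
| 12 | 7.716 | 64.3% |

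Whole trial as planned: 20 × 6.532 + 5.329 = 136.0 of 208, or 65.4%, against 104 (50%) by chance.

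**5. Would smaller fixed blocks help?** No. Certain allocations with a known fixed size would be 208 / 8 × 1.6 = 41.6 at size 8, 208 / 6 × 1.5 = 52.0 at size 6 and 208 / 4 × 1.333 = 69.3 at size 4. The weakness is that the size is fixed and known, not that it is ten.

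**6. Which varying sizes?** With the sizes in each mix equally likely:

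- 4, 6, 8: (2.833 + 4.100 + 5.329) / 18 = 12.262 / 18 = 68.1%
- 8, 10, 12: (5.329 + 6.532 + 7.716) / 30 = 19.577 / 30 = 65.3%

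The small mix makes guessing easier than the present plan does; the larger mix leaves it unchanged. Certainty falls sharply under both. In 1,500 simulated lists of 208, an observer who knew the possible sizes but not their order, and who saw every allocation, could be certain of about 5 allocations with 4, 6, 8 and about 3 with 8, 10, 12.

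**The case against.** The strongest reply is that the route to bias is inferred. The article specifies an independent statistician, opaque sealed envelopes in numbered order, allocation only after consent and baseline data, and a separate blinded assessor. It gives the facilitator no part in recruitment. A condensed article may leave delegation of staff to the full protocol, so silence about the screener is weak evidence that the roles overlap. Ten is already a large block, and one list across venues makes deduction harder for anyone who sees a single venue.

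Most of this stands. The figure of 35 is an expectation and needs sight of every earlier allocation in order. The facilitator sees who receives the intervention, but would also need the enrolment order to infer the controls. It does not remove the point, because the fixed size is stated in the text and the article takes care to separate the opener from the assessor but not from the screener.

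It is also true that varying the block size does not lower best-guess success. That strategy needs only the running totals, not the block size. Only separation of roles deals with it.

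A reader might go further and infer that the single list leaves recruitment source unbalanced, since Setting says: "Participants will be recruited from three acute public hospitals, and community-based organisations serving people with chronic conditions including stroke in Hong Kong". The documents do not support that. Randomisation balances source in expectation, and the usual standard error allows for chance differences. With an assumed 50:50 split of sources, the 95% range of the difference between arms is 1.96 × √(2 × 0.25 / 104) = ±13.6 percentage points. To turn this into a bias in the outcome, one must also assume how far the sources differ, for which the article gives no figure. Nor does it show that hospital recruits are recent and community recruits long past their stroke. The three hospitals share one stroke care pathway. Not stratifying is an acceptable choice.

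**Conclusion.** The concern holds as a weakness in allocation concealment that should be corrected; it is not a fatal flaw. Someone who knows the block size and all earlier allocations can be certain of about 35 of 208 on average, and can guess about 136 correctly where chance gives 104. The calculation assumes complete sight of the sequence, which the article clearly gives to the envelope opener alone.

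Whether any bias follows depends on that person, or someone they inform, influencing screening, consent or the timing of enrolment. The article neither states nor excludes this. One might read the figures as showing that allocation is compromised or that the facilitator can predict it; the text supports neither reading. No finding is made on balance by recruitment source.

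**What to change.** 1. For envelopes not yet used, have the independent statistician regenerate the list with randomly varying block sizes that are not disclosed to staff or stated in public documents while recruitment runs. Use larger sizes, for example 8, 10 and 12, rather than 4, 6 and 8.
2. State that the research assistant who opens the envelopes and the facilitator take no part in screening, consent or scheduling. This is the more important change, because it is the only one that also protects against guessing from the running totals. If the roles are already separate, one sentence is enough.

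The cost is a new list, a new set of unused envelopes and possibly an incomplete final block, so that the arms may differ slightly from 104 each. Separating the roles may also need a different member of staff for one task. No stratification is requested; hospital versus community source could at most be an optional covariate.

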### Intervention

The NSI aims to promote community reintegration of young stroke survivors and is designed on the basis of Narrative Theory [24] and Bandura’s principles of Self-efficacy and Outcome Expectation [25]. The NSI will consist of eight face-to-face sessions (1.5–2 h each) to be delivered over 24 weeks by a registered nurse (facilitator). The NSI will blend narratives and skills-building in each session to support participants’ reintegration into their post-stroke social roles. The narrative part will elicit the participants’ narratives of their experiences of engaging in everyday social activities including social, leisure and work activities, and will be used to identify the participants’ strengths, co-construct meanings of their experiences, re-structure self-identity and social roles, envision the future and explore opportunities for change. The skills-building part will develop the participants’ abilities to apply the life skills learned in order to maintain health and sustain their engagement in social activities. Three types of life skills will be included: self-management (goal setting, action planning, decision making, communication and utilisation of resources), outcome-expectation enhancing (reflection, solution focused) and self-efficacy enhancing (mastery, modelling, persuasion and reinterpretation of physical and emotional arousal) [12–20, 23].

Each session will have an assigned themed topic to articulate the narratives and skills-building. Each session is designed with a theme-related activity to arouse the participants’ interest in narrating their experiences and discussing the assigned themed topic. Strategies informed by the theoretical framework and tailored to young stroke survivors’ health needs will be adopted. The first three sessions will be foundational and conducted at the participants’ home bi-weekly to engage the participants in applying the skills learned to perform everyday household and social activities. The participants’ family members or caregivers will be invited to join these sessions. The remaining five sessions will be reintegration-enhancement sessions conducted in a private room at a community centre once every three weeks. These sessions will encourage the participants to address their struggles while reconstructing their self-identities and social roles. Each participant will be provided with a workbook with age-appropriate quick references for their narration and skills-building. Each participant will be given an online account to record their goals, action plans and daily accomplishments, and to retrieve 15 videos of other young stroke survivors sharing their experiences of reintegrating into social roles.

An expert panel consisting of two academics, one physician, one nurse consultant, two ward managers and one social worker will review the contents of the NSI. Their feedback will be incorporated in further revisions if deemed necessary. The revised NSI will be piloted with 10 potential young stroke survivors to assess their satisfaction and acceptability. Revisions will be made with consideration of the survivors’ feedback.

